### 2.3. Primary End Point

Five-millimeter space closure: To determine the successful outcome of the 3D and thermoformed aligners, a 5 mm of space closure is considered a successful outcome.Debris Index: (The buccal scores) + (The lingual scores)/(Total number of examined buccal and lingual surfaces).Calculus Index: Calculus Index = (The buccal scores) + (The lingual scores)/(Total number of examined buccal and lingual surfaces).Oral Hygiene Index simplified (OHIS): OHIS estimates the extent and amount of debris and calculus present on the tooth in each quadrant of the mouth. It demonstrates the oral hygiene status of the mouth. It is estimated using the debris index and calculus index provided by Greene and vermillion (1964).Plaque Index: The plaque index estimates the amount of plaque on the tooth surface in each quadrant. 0—Absence of plaque, stain or debris; 1—plaque covering no more than 1/3rd of tooth surface; 2—subtle plaque more than 1/3rd but not more than 2/3rd; 3. Plaque cover more than 2/3rd of the tooth surface.Bleeding Index: A modified Sulcus Bleeding Index (mSBI) will be used to record the bleeding from the sulcus and to determine the inflammation, as it is the early indicator of inflammation (clinically).Basic periodontal examination index (BPE): Periodontal status will be determined using the BPE scoring.Root Resorption: Basic periodontal examination such as hard tissues will be conducted using a combination of bitewing and peri-apical radiographs following selection criteria for dental radiography guidelines.Biofilm/Saliva: Saliva (Protease activity in saliva) to determine the immune-inflammatory processes by ELISA and biofilm (protease activity) by polymerase chain reaction (PCR).Oral microbiome: A standard estimation of the oral microbiome will be carried out using 16S ribosomal RNA gene sequencing analysis.

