## Abstract

Aligners are the common devices used in orthodontics for the correction of malocclusion. Various materials and techniques are employed to fabricate aligners. One of those includes thermoformed and 3D aligners. These aligners can be worn for several days, and their impact on periodontal health is not known. Therefore, the aim of our protocol is to determine the effectiveness of these aligners in correcting malocclusion and their impact on periodontal health and oral microbiome. A double-blinded randomized controlled clinical trial with a total of *n* = 60 patients will be included with *n* = 30 in each group (Test: 3D printed aligners and Control: Thermoformed). The evaluation of oral health indices such as basic periodontal examination (BPE), periodontal screening and recording (PSR) that provide the status of periodontal health will be recorded. The oral microbiome assessment will be conducted with polymerase chain reaction (PCR). The primary endpoint will be the correction of malocclusion, and the secondary end point will be the status of periodontal health and oral microbiome. The duration of follow-up for each group will be 7 days for periodontal health and oral microbiome and 6 months for the space closure of 5 mm by 3D and thermoformed aligners.

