### 1.1. Aim 1: Effectiveness and Efficacy of Clear Aligners (Invisalign) in Correcting Malocclusions

The clear aligners were introduced in the 1940s, but due to lack of evidence and promotion, it was not widely practiced and adopted. Later, due to the development of biomaterials in dentistry and 3D technology, it became very much popular. Recently, there have been more expert opinions in favor of clear aligners, and there is a lack of evidence in correcting a wide range of malocclusions [21]. Not many studies described the effectiveness of treatment with 3D and thermoformed clear aligners and its impact on periodontal health, generating doubts among clinicians on the efficacy of the device.

Therefore, a well-designed parallel randomized controlled clinical trial will help to overcome the problem. The spacing >5 mm correcting it by using 3D clear aligners and compared with thermoformed aligners therapy.

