### 2.2. Trial Design

We propose to conduct a double-blinded randomized controlled clinical trial in patients who have >5 mm of spacing in both maxilla and mandible and cases with skeletal class I coming to the department of Orthodontics and Dentofacial Orthopaedics at Fondazione IRCCS Cà Granda Ospedale Maggiore Policlinico di Milano, SST clinics and Università degli Studi di Bari and Naples Clinica Odontoiatrica. Patients in both arms will receive adhered support and will be monitored more frequently than currently recommended by WHO guidelines. The first arm will undergo a traditional method of managing of closure of spacing by thermoformed aligners, and the second aim will be treated with thermoformed and 3D printed aligners. Eligible patients are randomized to the control arm or the intervention arm with a 1:1 ratio using a blocked randomization scheme. The patients will be followed for 6 months (Figure 1).

There will be an initial assessment with detailed case history, extra-oral and intra-oral examination, and clinical radiographs. A diagnosis and treatment plan will be framed. Pre- and post-operative samples of biofilm and saliva will be collected to determine the inflammatory and immunological response. The bridging and early colonizers such as *Fusobacterium nucleatum* (*F. nucleatum)*, pathogenic species such as *Porphyromonas gingivalis (P. gingivalis)*, microbial communities and the composition of the biofilm will be determined by ELISA and PCR. This will help to answer the questions such as if any infection is present, which bacteria colonize, whether we should use antibiotics, etc. In addition, 16 s-ribosomal RNA signatures for identification of the microbial composition of biofilm structures.

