***Baseline information:*** (1) A Patient Measured Outcome Questionnaire (PROM) was completed to determine the impact of oral health on quality of life. The PROMs are dozens of tools that allow you to measure the important results for the patient, for example, cost, symptom relief, quality of care, improved oral health, and overall health. It is evaluated after each intervention. (2) Numerical rating scale (NRS) for measuring the pain of patients before and after the intervention. (3) Periodontal health status will be assessed by basic periodontal examination (BPE), Periodontal screening and recording index (PSR index), Basic Periodontal Examination (BPE) scores, Oral Hygiene Index simplified (OHIS), Saliva (Protease activity in saliva) to determine the immune-inflammatory processes by ELISA and biofilm by polymerase chain reaction (PCR). ***Inclusion criteria:*** The eligible cases will be identified during routine clinical visits. CAT is indicated in cases of slight crowding (1–5 mm), spacing problems (1–5 mm), deep overbites (Class II, div. 2), narrow arches requiring expansion, absolute intrusion (one or two teeth), severe crowding with the extraction of the lower incisor and molars requiring distal tipping. Contraindications are crowding and spacing problems greater than 5 mm, anterior-posterior skeletal problems greater than 2 mm, relationship discrepancies and centric occlusion, severely rotated and inclined teeth, open bite, dental extrusion cases, cases with more missing teeth and teeth with short clinical crowns.

Written informed consent will be obtained before the inclusion of the study. An entry form will be completed to determine the eligibility and to collect the baseline characteristics such as periapical radiographs, panoramic radiographs, models, casts, cephalometric tracings, CBCT scans, etc. Patients will be randomized in thermoformed and 3D clear aligners. All non-extraction cases except third molar extraction will be included. ***Exclusion criteria:*** Patients with deciduous and mixed dentition will not be included, and patients with systemic disease, developmental abnormalities, pregnant patients, mentally retarded patients and immunocompromised patients will not be included in the study.

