## 3. Statistical Analysis

The sample size was calculated using a two-sided test by comparing two independent means of control and test between groups with a statistical power of 0.80, alpha of 0.05, with an allocation ratio of 1:1 using STATA 17.0 statistical software. The mean of space closure of 3 mm in control and 5 mm in the test group with sd for control 2.5 and test 2.0 demonstrated that a sample of a least 22 subjects for both groups must be recruited (a total of 44 patients should be recruited). In order to compensate for the loss of follow-up, an increase in patient number *n* = 70 will be recruited.

A descriptive statistic will be carried out for all the indices before and after intervention with 3D and thermoformed aligners. If the data are normally distributed, a parametric test will be carried out. The non-parametric test will be used for the analysis of data that are not normally distributed. A regression analysis to determine the relationship between the dependent and independent variables and for modeling the future relationship between them.

***Safety measurements and adverse events:*** All patients will be monitored for general health and for serious adverse events related to the drug intervention. General and oral assessment including weight, blood pressure, pulse rate, skin, lymph node size, and thyroid palpation will be recorded. There will be no compensation for any adverse events or withdrawal from the study.

***Challenges and Limitations: Follow-up:*** There are chances that there will be a loss of compliance from the patient. To overcome this problem, the patient will be educated and will increase awareness in regard to the type of treatment receiving and its impact on aesthetics.

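### A flat 5 mm success rule, tied to neither baseline nor residual space, does not measure correction and fits neither of the stated spacing ranges

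*Protocol article*

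**What the plan says.** Section 2.3 gives one efficacy success rule: "a 5 mm of space closure is considered a successful outcome". It names no unit (site, arch or mouth) and sets no requirement on the space that remains. The Abstract describes the same endpoint in two ways: "The primary endpoint will be the correction of malocclusion", and a follow-up of "6 months for the space closure of 5 mm by 3D and thermoformed aligners".

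The baseline spacing to which the rule applies is stated inconsistently:

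- Section 1.1 (Aim 1): "The spacing >5 mm correcting it by using 3D clear aligners".
- Section 2.2, opening paragraph: "patients who have >5 mm of spacing in both maxilla and mandible".
- Section 2.2, inclusion criteria: spacing of 1–5 mm is listed as an indication, followed by "Contraindications are crowding and spacing problems greater than 5 mm".

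Section 3 plans on a continuous measure: "The mean of space closure of 3 mm in control and 5 mm in the test group with sd for control 2.5 and test 2.0". It does not say whether these millimetres are per arch or per mouth.

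**The concern.** A success rule should separate patients whose problem was resolved from those whose problem was not. A fixed number of millimetres closed does this only if everyone starts with that amount of space, and no passage says so. Where patients start above 5 mm, the rule accepts incomplete closure, and the share of space that must be closed falls as the baseline rises. Where an arch starts below 5 mm, a rule counted per arch rejects complete closure.

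At stake is the interpretation of the result. A report that a given share of patients had a successful outcome, read alongside the Abstract as correction of malocclusion, would partly describe how much space patients had at entry and how the arches were added up.

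**Working it through.** **1. The plan's own figure.** Inputs from Section 3: means 3 and 5 mm, SDs 2.5 and 2.0, two-sided alpha 0.05, power 0.80, allocation 1:1.

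- Pooled SD = √((2.5² + 2.0²)/2) = 2.264; difference = 5 − 3 = 2 mm.
- The normal approximation gives 21 per group.
- The t-based calculation with unequal SDs gives power 79.7% at 21 and 81.6% at 22 per group.

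The stated 22 per group (44 in total) therefore reproduces. It rests on a difference in means, and the success threshold does not enter it.

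**2. Baseline above 5 mm, counted per arch.** Residual = baseline − 5; share to be closed = 5 / baseline. The baselines are my assumptions; the article gives no distribution.

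| Baseline in the arch | Left open at exactly 5 mm closed | Share that must be closed |
|---|---|---|
| 5.5 mm | 0.5 mm (9%) | 91% |
| 7 mm | 2 mm (29%) | 71% |
| 9 mm | 4 mm (44%) | 56% |

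The test-group mean planned in Section 3 equals the threshold. A patient who starts above 5 mm and achieves exactly that mean is a success with space remaining.

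**3. Baseline above 5 mm in each arch, counted per mouth.** The mouth total T then exceeds 10 mm. If 5 mm is a mouth total, 5/T is below 50% and T − 5 is above 5 mm. If 5 mm is required in each arch, the bar is 5 + 5 = 10 mm, a ratio of 2. For an assumed 6 + 6 = 12 mm:

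- Mouth-total rule: 5/12 = 42% closed, 7 mm (58%) open.
- Each-arch rule: 10/12 = 83% closed, 2 mm open.

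**4. Baseline of 1–5 mm, counted per arch.** The most an arch with baseline b can close is b. If b is below 5, complete closure gives b < 5, which is not a success.

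**5. How far the counting rule could move a success proportion.** This is an illustration that assumes normal closure with the Section 3 means and SDs. The model is rough, since closure cannot exceed the space available.

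- If those figures are mouth totals: at least 5 mm is reached by 21% of controls and 50% of test patients. At least 10 mm, the minimum that an each-arch rule implies, is reached by 0.3% and 0.6%.
- If they are per arch, with between-arch correlation from 0 to 0.9: a sum of at least 5 mm is reached by about 58–61% and 90–96%; at least 5 mm in each arch by about 4–16% and 25–43%.

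**6. What a complete-closure rule would give.** Same model, figures taken per arch, assumed 7 mm baseline. Test: (7 − 5)/2.0 = 1.0 SD above the mean, about 16% of arches. Control: (7 − 3)/2.5 = 1.6 SD, about 5%. Requiring both arches cannot raise these.

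**The case against.** **The population above 5 mm is one side of an unresolved conflict.** This stands. The inclusion criteria in Section 2.2 make spacing above 5 mm a contraindication, so it would be wrong to say that entry has no upper limit. The residuals in steps 2 and 3 apply only if the wording of Section 1.1 and the trial-design paragraph holds. The point survives because the rule also fails under the other range, in the opposite direction.

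**No analysis of a success proportion is described.** This also stands. A reader might infer that the treatment comparison is biased or the trial wrongly sized. The article does not support that: Section 3 sizes the trial on mean millimetres closed, and patients are randomised 1:1 in blocks. The defect concerns what the label means.

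**Counting detail may sit in a fuller protocol.** That is possible for the unit. It does not answer the main point, because the flat threshold is itself stated and disregards baseline whatever the unit. A reader might also infer that clinics would score the same result differently. Nothing says that clinics apply rules of their own, so this would be conjecture.

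**The two-fold shift is conditional.** It needs more than 5 mm in each arch and a rule requiring 5 mm in both. If the wording in Section 2.2 means a combined total, closing exactly 5 mm still leaves some space, but not necessarily in both arches. The claim that successes generally keep open spaces in both arches therefore goes too far. How many patients would be misclassified cannot be derived.

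**Section 2.3 says successful, not corrected.** That is true, and the phrase might mean closing a 5 mm gap. The text does not say so, it would not fit a baseline above 5 mm, and the Abstract joins the two ideas.

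**Conclusion.** The concern holds in limited form. A flat 5 mm closed does not measure correction of malocclusion under either stated spacing range. Above 5 mm it can be met with space open (0.5, 2 or 4 mm per arch at assumed baselines of 5.5, 7 or 9 mm; 7 of 12 mm at an assumed 6 + 6 mm counted per mouth). Below 5 mm, counted per arch, full closure cannot meet it. If more than 5 mm in each arch is meant, the whole-mouth bar is 5 or 10 mm according to a counting rule that the article does not give.

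The subtraction is certain; the example baselines and the normal model are assumptions. The comparison of means and the sample size in Section 3 are sound in this respect. The change is worth making because it settles what the trial may claim about success and correction.

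**What to change.** 1. Reconcile the spacing ranges in Section 1.1, the trial-design paragraph of Section 2.2 and the inclusion criteria of Section 2.2. State whether the range applies to each arch or to the mouth. Which range applies is for the investigators to settle.
2. In Section 2.3, state one counting unit, for example per arch and averaged per patient. Keep millimetres closed at 6 months as the main continuous measure, and say in Section 3 that the 3 and 5 mm are in that unit.
3. Report residual space and percent of baseline space closed at 6 months beside it.
4. Do not describe 5 mm closed as correction unless the criterion is tied to residual space.

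The cost is mostly wording. Spacing must be measured on comparable records at baseline and at 6 months. The article lists models and casts as baseline items, and any 6-month closure measure needs a follow-up record in any case. A success proportion tied to residual space will be lower, possibly much lower (step 6 of the working), with little information at about 22 per group. It should therefore support the continuous measure and not replace it.

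### Section 2.3 assigns biofilm protease activity to PCR, which reads nucleic acid and cannot measure enzyme activity, so this endpoint component has no assay that yields it

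*Protocol article*

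**What the plan says.** Section 2.3 (Primary End Point) of the protocol article treats Biofilm/Saliva as one item with two halves. The saliva half reads "Saliva (Protease activity in saliva) to determine the immune-inflammatory processes by ELISA". The biofilm half reads "biofilm (protease activity) by polymerase chain reaction (PCR"). The next item, oral microbiome, is separate: "A standard estimation of the oral microbiome will be carried out using 16S ribosomal RNA gene sequencing analysis".

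Other parts of the article describe the same specimens as follows.

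- Section 2.2, main text: "microbial communities and the composition of the biofilm will be determined by ELISA and PCR". The sentence names *F. nucleatum* and *P. gingivalis* as examples. The paragraph then adds, as a further step, "16 s-ribosomal RNA signatures for identification of the microbial composition of biofilm structures".
- Section 2.2, baseline information: "to determine the immune-inflammatory processes by ELISA and biofilm by polymerase chain reaction (PCR"). No analyte is named for biofilm.
- Abstract: "The oral microbiome assessment will be conducted with polymerase chain reaction (PCR").

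**The concern.** An endpoint needs an analyte and a method that measures it. Here both are stated, and they do not fit. PCR amplifies nucleic acid. It can show that an organism or a protease gene is present and how abundant it is, or, with reverse transcription, that a transcript is present. It does not show whether a protease is active or how strongly.

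Biofilm and microbiome belong to the trial's second aim (Section 1.2). If Section 2.3 is followed literally, the biofilm protease result is either absent or consists of nucleic-acid data under an enzyme-activity label. The second outcome would be a poor basis for any statement about inflammation under the two aligner types.

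**Working it through.** No figure is in dispute, so the check is a comparison of the text, followed by a look at how far the defect reaches.

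**1. Analyte and assay, place by place**

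| Place | Specimen or outcome | What is measured | Assay |
|---|---|---|---|
| Section 2.3 | Saliva | Protease activity | ELISA |
| Section 2.3 | Biofilm | Protease activity | PCR |
| Section 2.3 | Oral microbiome | Not spelled out further | 16S rRNA gene sequencing |
| Section 2.2, main text | Biofilm | Organisms, communities, composition | ELISA and PCR, plus 16S rRNA |
| Section 2.2, baseline | Biofilm | Not named | PCR |
| Abstract | Oral microbiome | Not named | PCR |

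**2. The biofilm row of Section 2.3.** The analyte is an enzyme activity and the assay reads nucleic acid. No second assay is attached to biofilm in that item, so nothing in the definition can supply the value.

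**3. Comparison with Section 2.2.** The main text pairs PCR with organisms and composition, which PCR can address. The baseline paragraph has almost the same sentence as Section 2.3 but without the protease wording for biofilm. It is silent on the analyte and so cannot settle which construct was meant.

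**4. The microbiome rows.** Section 2.3 gives one definition, 16S sequencing. Section 2.2 presents 16S as additional to ELISA and PCR. Only the abstract names PCR alone.

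**5. Reach.** Section 2.3 lists ten items: space closure, debris index, calculus index, OHIS, plaque index, bleeding index, BPE, root resorption, Biofilm/Saliva and oral microbiome. The mismatch affects half of the ninth.

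The only sample-size calculation (Section 3) is for space closure: 3 mm against 5 mm, SDs 2.5 and 2.0, two-sided alpha 0.05, power 0.80. It reproduces:

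- Pooled SD = √((2.5² + 2.0²)/2) = √5.125 = 2.264.
- Normal approximation: n = 2 × (1.960 + 0.842)² × 5.125 / 2² ≈ 20.1, so 21 per group.
- Unequal-variance t-test: power 0.797 at 21 per group and 0.816 at 22, so 22 per group, as stated.

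Nothing in that calculation uses a protease, biofilm or microbiome quantity, so the powered comparison is unaffected.

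**The case against.** Four points can fairly be made against the concern.

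- **The microbiome assays need not compete.** A reader might infer that the microbiome outcome has two rival definitions, and that whichever favours an arm could be reported. The documents do not support this. Section 2.2 declares 16S as an addition, Section 2.3 gives a single definition, and 16S sequencing normally includes a PCR step, so the abstract may simply be using shorthand. What remains is imprecise wording in the abstract.
- **Section 2.2 does not flatly contradict Section 2.3.** The baseline paragraph names no analyte for biofilm. The main text also says that biofilm and saliva are sampled to study the inflammatory and immunological response, which leaves room for a biofilm protease measure. This stands: the two sections differ in what PCR is used for, but silence on protease does not exclude it.
- **The rank is uncertain.** Section 2.3 lists the item as primary, while the abstract makes malocclusion correction primary and ranks periodontal health and the microbiome as secondary. This limits the weight of the point, but an outcome that cannot be measured needs correcting at either rank.
- **The protease wording may be a slip.** Possibly, but it sits inside an endpoint definition. A fuller protocol could add missing detail; it would not make the stated pairing valid.

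None of these supplies a way to obtain enzyme activity from PCR.

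**Conclusion.** The point holds in a narrow form. The biofilm half of the Biofilm/Saliva item in Section 2.3 is defined by an assay that cannot yield it. This is a stated mismatch, not detail left to another document. It concerns half of one of ten listed items, leaves the powered space-closure endpoint untouched, and is cheap to correct.

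The conclusion rests on one piece of general laboratory knowledge, that PCR reads nucleic acid and not enzyme activity, and on reading PCR as the assay for the biofilm protease named directly before it.

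Two stronger readings go beyond the text. One is that species counts would in fact be reported as protease activity; nothing in the article says so. The other is that bacterial load was clearly the intended construct. The article does not show whether the sponsor wanted bacterial load or protease activity in biofilm.

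**What to change.** In Section 2.3, match analyte and assay for biofilm in one of two ways. The choice is the sponsor's.

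1. **Delete the protease wording for biofilm** and define the item as PCR detection or abundance of prespecified organisms, in line with Section 2.2. The two species named there are introduced as examples, so the list must be fixed explicitly. No new assay is needed; the cost is that the biofilm protease claim is dropped.
2. **Keep biofilm protease activity** and name an assay that measures it. This preserves the construct; the cost is an assay that the article does not currently name for biofilm, with whatever sample handling it needs.

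Either way, carry the same wording into the baseline paragraph of Section 2.2. As a minor consistency edit, change the abstract so that the oral microbiome is assessed by 16S rRNA sequencing as in Section 2.3, with any targeted PCR reported separately. In the same pass, state the rank of these items consistently between the abstract and Sections 2.3 and 2.4.
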